### Interventions

2.9

#### Run-in period

2.9.1

All participants will be treated with metformin and/or alpha-glucosidase inhibitor and/or insulin to control hyperglycemia, angiotensin-converting enzyme inhibitors (ACEI) and/or angiotensin receptor blockers (ARB) and/or calcium channel blockers (CCB) and/or Thiazide-like diuretic to control hypertension, aspirin to inhibit platelet and atorvastatin to regulate dyslipidemia before entering the treatment period. After a 4-week's run-in period, participants’ blood glucose, blood lipid and blood pressure must meet the following criteria before entering the treatment period. If people under the age of 65 years, the following criteria must be met:

(1)FPG between 4.4 mmol/L and 7.0 mmol/L, and non-fasting blood glucose <10.0 mmol/L;(2)blood pressure ≤130/80 mmHg;(3)low-density lipoprotein cholesterol ≤2.6 mmol/L.

If people over the age of 65 years, the following criteria must be met:

(1)FPG between 5.0 mmol/L and 8.3 mmol/L, and non-fasting blood glucose <11.1 mmol/L;(2)blood pressure ≤140/90 mmHg;(3)low-density lipoprotein cholesterol ≤2.6 mmol/L.

#### TCM intervention

2.9.2

The study has 2 arms. The WM conventional treatment of controlling hyperglycemia contain metformin and/or alpha-glucosidase inhibitor and/or insulin. ACEI and/or ARB and/or CCB and/or Thiazide-like diuretic are selected to control hypertension, aspirin to inhibit platelet and atorvastatin to control hyperlipidemia. After enrollment, participants will be randomized to either groups:

(1)the treatment group (n = 60), participants will take CHM Shen-Qi Hua-Yu granules, which is composed of Renshen (Ginseng), Zhihuangqi (Astragalus membranaceu), Shanzhuyu (Asiatic Cornelian Cherry Fruit), Shengdihuang (Unprocessed Rehmannia Root), Shuizhi (Leech), Dilong (Earthworm), Jixueteng (Suberect Spatholobus Stem), Taoren (Peech Seed), Honghua (Carthamus Tinctorius), Niuxi (Twotoothed Achyranthes Root);(2)the placebo group (n = 60). The action of each herb is summarized in Table 1. The treatment course is 12 weeks.

**Table 1 T1:**
[figure not shown]
The action of each Traditional Chinese Medicinal herb.

In order to stabilize the formulation, increase the convenience of taking medicine, remove the influence factors such as the method of decocting and the origin of medicinal materials, and facilitate the observation and blind implementation, the study adopted the preparation of granules. The placebo is made from dextrin, food colorants, bitters, and water. Placebo and Shen-Qi Hua-Yu granules are close to the same in color, smell, taste, appearance, packaging, and tag. They are prepared by Sichuan green pharmaceutical technology development Co. Ltd, Sichuan, China.

Participants will dissolve granules into 100 ml of hot water, cover and seal for 3 to 5 minutes, then take it between 30°C and 36°C. Each time 1 bag of granules, 3 times a day.

### Outcome measures

2.10

#### Primary efficacy outcomes

2.10.1

ABI will be measured before treatment and after 12-week treatment and every 12 weeks during follow-up observation, 6 times in total. ABI will be measured and calculated using blood pressure cuff and continuous waveform doppler probe.

#### Secondary efficacy outcomes

2.10.2

The color Doppler ultrasound will detect the inner diameter, peak systolic velocity (PSV), end diastolic velocity (EDV) and mean average velocity (Vm) of the anterior tibial artery, posterior tibial artery and dorsalis pedis artery of the patients will be detected. The pulse index (PI) and resistance indices (RI) will be calculated according to the formula. PI = (PSV-EDV)/Vm, RI = (PSV-EDV)/PSV. It will be measured before and after 12 weeks of treatment and every 24 weeks during the follow-up observation, 4 times of measurement in total.

Other secondary efficacy outcomes include changes in FPG, total cholesterol, triglycerides, high-density lipoprotein cholesterol, low-density lipoprotein cholesterol, homocysteine, hemorheology indexes (plasma viscosity, whole blood viscosity, hematocrit, erythrocyte aggregation index, erythrocyte rigidity index, fibrinogen, erythrocyte sedimentation rate, equation K value of erythrocyte sedimentation rate), advanced glycation end products, and TCM syndrome score measured by questionnaire. All of these will be measured before and after 12 weeks of treatment, 2 times in total. Three to 4 ml venous blood will be collected for each detection.

#### Therapeutic mechanism outcomes

2.10.3

The study will use iTRAQ to quantify detection and analyze the serum protein of participants before and after treatment and then determine it by western blot.

#### Endpoint outcomes

2.10.4

The endpoint incidents are defined as major adverse cardiovascular events that including cardiovascular death, myocardial infarction and ischemic stroke, or complete occlusion of the blood vessels, or ulcer, or gangrene of the lower limbs. In this study, the incidence of endpoint incident and the time of progression to endpoint incident will be selected as the indicators.

#### Safety outcomes

2.10.5

Safety will be monitored using blood, urine and stool routine examination, liver function (alanine aminotransferase, aspartate aminotransferase, total bilirubin, alkline phosphatase, glutamyl transpeptidase), renal function (blood urea nitrogen, creatinine) and electrocardiogram. The researchers should record the occurrence and nature of each participant's pre-existing conditions, including clinically significant signs and symptoms of the disease being treated during the study. All adverse events related to medicine will be immediately reported in written Case Report Forms to the Ethical Review Committee of Hospital of Chengdu University of Traditional Chinese Medicine and each participating center.

### Sample size

2.11

The study is an optimality trial, and the control group is placebo group. ABI is the primary outcome, and setting the optimum value to 0.04 based on the response rates of treatment. According to previous clinical research data, the mean value between the 2 groups is 0.13, and the standard deviations of treatment group and control group are 0.19 and 0.11 respectively. Set α to 0.025 and β to 0.2. Used PASS 11 software to calculate the sample size of each group is 48. Meanwhile, taking into account a dropout of 20% and according to the formula that is n^ = n / (1–f), we concluded that in order to ensure statistically significant results, the total number of study samples is determined to be 120 cases with 60 for each group.

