### Statistical analysis

2.12

The statistical analysis of this study will be conducted by statisticians of the Sichuan University. They will use Statistical Analysis software packages SPSS 23.0 and SAS 9.1. Demographic and other baseline characteristics will analyze using the full analysis set (FAS). Full analysis set will analyze with intention-to-treat (ITT), and per-protocol set (PPS) will statistically analyzed. Safety analysis will be performed according to safety data set for subjects who receive at least 1 treatment after randomization. Normally distributed data is represented by mean ± standard deviation, and non-normally distributed data is represented by median and interquartile range. Comparisons between groups of measurement data will be conducted by using independent-sample *t* test, and within group differences will be tested with paired *t* test. Differences between groups of numeration data will be assessed with chi-square test. Comparison of survival rate and survival time between groups will be analyzed by Kaplan–Meier curve to explore each possible relevant factor. Covariates were then included in the multi-factor Cox regression model for analysis to detect the influence of these variables on end event of the study. This study is a multi-center clinical trial. CMH χ2 will be used for numeration data, analysis of variance (ANOVA) and an analysis of covariance (ANCOVA) will be used for measurement data, and log-rank test will be used for endpoint outcomes. After deducting the influence of polycentric effect, comparing efficacy outcomes, endpoint outcome index and safety outcomes between 2 groups.

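### The trial is sized for superiority by a margin of 0.04 ABI, but the analysis section names ordinary tests without the margin, so the stated power and sample size do not describe the named test

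*Protocol article*

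**What the plan says.** The protocol article, section 2.11 (Sample size), describes the trial type as follows: "The study is an optimality trial, and the control group is placebo group". It fixes a value of 0.04 for ABI: "ABI is the primary outcome, and setting the optimum value to 0.04 based on the response rates of treatment". It then gives the planning assumptions:

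- difference: "the mean value between the 2 groups is 0.13"
- variability: "the standard deviations of treatment group and control group are 0.19 and 0.11 respectively"
- error rates: "Set α to 0.025 and β to 0.2"
- result: "Used PASS 11 software to calculate the sample size of each group is 48", raised to 60 per group (120 in total) for 20% dropout.

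Section 2.12 (Statistical analysis) assigns one method to all continuous outcomes: "Comparisons between groups of measurement data will be conducted by using independent-sample" t test. It adds ANOVA and ANCOVA for measurement data to allow for centre. It does not mention 0.04, a null value, or a confidence limit to be compared with a margin.

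**The concern.** The two sections appear to address different hypotheses. Section 2.11 sizes a test of whether the formula beats placebo by more than 0.04 ABI. Section 2.12 names tests which, without further qualification, ask whether the difference is anything other than zero. The same unmodified t test is applied to ABI and to glucose, lipids and viscosity, none of which has a margin.

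At stake is what a positive primary result means. If the margin is intended, a significant ordinary t test does not establish the hypothesis for which 120 patients were justified. If it is not intended, the stated 80% power and 48 per group belong to a test that will not be done.

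**Working it through.** **Inputs (section 2.11).** Expected difference 0.13; margin 0.04; SDs 0.19 and 0.11; alpha 0.025; power 0.80. The article does not say whether alpha is one- or two-sided.

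**Step 1: reproduce the plan's figure.** Sum of variances = 0.19² + 0.11² = 0.0361 + 0.0121 = 0.0482. With a margin, the net effect is 0.13 − 0.04 = 0.09.

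Normal approximation: n per group = (1.960 + 0.842)² × 0.0482 / 0.09² = 46.7, rounded up to 47. The noncentral t calculation (Welch) gives 48, with power 0.801. Dropout: 48 / (1 − 0.20) = 60 per group, 120 in total. All of the plan's figures are reproduced.

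**Step 2: try the other readings.**

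| Null value | Alpha 0.025 read as | n per group, normal | n per group, t |
|---|---|---|---|
| 0.04 (net 0.09) | one-sided | 47 | **48** |
| 0.04 (net 0.09) | two-sided | 57 | 58–59 |
| 0 (difference 0.13) | one-sided | 23 | 24 |
| 0 (difference 0.13) | two-sided | 28 | 29 |

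Of these readings, only a 0.04 margin at one-sided 0.025 gives 48.

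**Step 3: what the sample size delivers against zero.** At one-sided 0.025 and a true difference of 0.13, power (Welch) is:

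| n per group | Power against zero | Power against 0.04 |
|---|---|---|
| 48 | 0.982 | 0.801 |
| 60 | 0.995 | 0.882 |

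A test against zero would need 24 per group, or 24 / 0.8 = 30 randomised per group and 60 in total.

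**Step 4: where the two tests disagree.** The standard error with 48 per group is √(0.0482 / 48) = 0.0317. The smallest observed difference significant against zero is the t critical value times this standard error, about 0.063. Significance against the margin needs 0.04 + 0.063 = 0.103. With 60 per group the limits are 0.056 and 0.096. If the true difference is 0.13, the chance of a result significant against zero but not against 0.04 is 0.982 − 0.801 = 0.181 at 48 per group, and 0.995 − 0.882 = 0.113 at 60 per group.

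These limits use the unadjusted t test and the planning SDs, so they are only approximate for a centre-adjusted ANCOVA.

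**The case against.** The strongest reply is that section 2.12 writes out no null value. A t test or an ANCOVA contrast can be judged against 0.04 as easily as against zero, and a condensed article may leave the decision rule to a fuller document. This stands in part: that the test is against zero is an inference and not a stated fact. It is nevertheless the ordinary reading of a test named without qualification and applied alike to outcomes that have no margin. Section 2.12 is not merely silent. It names the between-group test, and that test as usually understood is not the one sized in 2.11.

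Three stronger readings are tempting, and the article does not support them.

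- **Inflated false-positive rate.** A reader might note that if the true difference were exactly 0.04, a test against zero would be significant in about 24% of trials at 48 per group (29% at 60), and set this against 2.5%. But at a true difference of 0.04 there is a real effect, so rejecting zero is correct, and that test keeps its 2.5% one-sided error. The 24% is an error rate only for the separate claim of superiority by more than 0.04.
- **A false claim of success.** No section defines success or says how a significant result would be described. The Introduction's aim is to learn whether the formula is effective and safe, which a test against zero can address.
- **Too few patients.** The reverse holds: 48 per group is adequate for the margin test and twice what a test against zero needs.

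The appeal to response rates as the basis for a margin on continuous ABI is a separate question, and this point does not rest on it.

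**Conclusion.** The point holds as a mismatch between two sections. The sizing half is firm: on the article's own inputs, 48 per group is the answer to a superiority test with a 0.04 margin at one-sided 0.025. The analysis half rests on the usual reading of an unqualified t test and ANOVA/ANCOVA as tests of zero.

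On that reading, the stated 80% power should be about 98%, the required 48 per group should be 24, and unadjusted results between about 0.063 and 0.103 at 48 per group would be significant without showing what the trial was sized to show. The test against zero is neither invalid nor underpowered; it supports a weaker claim. The conclusion assumes the planning SDs and a one-sided alpha. The article does not state the sidedness, but the one-sided reading reproduces its figure.

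**What to change.** Before unblinding, the sponsor should choose one of two wordings.

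1. **Keep the margin.** State in 2.12 that the primary test is of H0: mean ABI difference (treatment minus placebo) ≤ 0.04 at one-sided 0.025, with success when the lower limit of the two-sided 95% confidence interval exceeds 0.04. The 48 per group and 80% power then stand. The cost is a stricter success criterion.
2. **Drop the margin.** Remove 0.04 from 2.11 and restate power against zero: about 98% at 48 evaluable per group for a true difference of 0.13. The cost is a changed power statement, and the article must then acknowledge that its inputs alone would require fewer patients.

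Either way, state in 2.11 that alpha is one-sided. The change is to wording only, and the 120 patients can stay as planned.

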### Statistical analysis

2.12

The statistical analysis of this study will be conducted by statisticians of the Sichuan University. They will use Statistical Analysis software packages SPSS 23.0 and SAS 9.1. Demographic and other baseline characteristics will analyze using the full analysis set (FAS). Full analysis set will analyze with intention-to-treat (ITT), and per-protocol set (PPS) will statistically analyzed. Safety analysis will be performed according to safety data set for subjects who receive at least 1 treatment after randomization. Normally distributed data is represented by mean ± standard deviation, and non-normally distributed data is represented by median and interquartile range. Comparisons between groups of measurement data will be conducted by using independent-sample *t* test, and within group differences will be tested with paired *t* test. Differences between groups of numeration data will be assessed with chi-square test. Comparison of survival rate and survival time between groups will be analyzed by Kaplan–Meier curve to explore each possible relevant factor. Covariates were then included in the multi-factor Cox regression model for analysis to detect the influence of these variables on end event of the study. This study is a multi-center clinical trial. CMH χ2 will be used for numeration data, analysis of variance (ANOVA) and an analysis of covariance (ANCOVA) will be used for measurement data, and log-rank test will be used for endpoint outcomes. After deducting the influence of polycentric effect, comparing efficacy outcomes, endpoint outcome index and safety outcomes between 2 groups.

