### Study visit

2.2

In this study, participants qualified for inclusion in this trial will be selected at the first visit, and will be well-prepared for the run-in period at the second visit, at last will be randomly assigned to TCM granules or placebo at the third visit. During the treatment period, participants will receive outpatient and telephone visits every 2 weeks. At the 2nd, 6^th^, and 10th weeks of treatment, the researchers will assess the participant's response to the drug through telephone visit. At the 4th, 8th, and 12th weeks of treatment, researcher will visit participants at the research settings and be evaluated according to the research schedule. After the end of the treatment period, participants will be followed up four times at the 12th, 24th, 36th, and 48th weeks. The researchers will evaluate the changes in the outcome of lower extremity artery effective measures from baseline. Each participant will be visited 13 times in this study.

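### Continuous outcomes, and so the primary ABI, are given both to an unadjusted t test and to ANOVA/ANCOVA without saying which decides; one ANCOVA on baseline ABI and centre should be named as primary

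*Protocol article*

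**What the plan says.** All of the analysis text is in one paragraph, section 2.12 (Statistical analysis) of the protocol article.

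- Early in the paragraph: "Comparisons between groups of measurement data will be conducted by using independent-sample" t tests.
- Later, after noting that the trial is multi-centre: "analysis of variance (ANOVA) and an analysis of covariance (ANCOVA) will be used for measurement data". No covariate is named for the ANCOVA.
- At the end: "After deducting the influence of polycentric effect, comparing efficacy outcomes, endpoint outcome index and safety outcomes between 2 groups".

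The section does not mention ABI by name. The link comes from section 2.11 (Sample size), which states that "ABI is the primary outcome", and from section 2.10.1 (Primary efficacy outcomes): "ABI will be measured before treatment and after 12-week treatment and every 12 weeks during follow-up observation, 6 times in total". ABI is therefore measurement data, and a baseline value is scheduled for every participant. Section 2.2 (Study visit) adds: "The researchers will evaluate the changes in the outcome of lower extremity artery effective measures from baseline". The sample size rests on "setting the optimum value to 0.04" and "the mean value between the 2 groups is 0.13".

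**The concern.** Two statements in one paragraph give the same class of data to different tests, and neither takes precedence. Three p-values for the primary outcome can follow from the text: t test, ANOVA and ANCOVA. If the deciding one is not fixed before unblinding, the favourable one can be reported.

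The paragraph also conflicts with itself. An independent-sample t test makes no allowance for centre, yet efficacy is to be compared with the centre effect removed, and section 2.6 (Recruitment) names three hospitals.

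Finally, the plan already names ANCOVA and already collects baseline ABI, but does not connect the two. If baseline and week-12 ABI are correlated, the primary comparison gives up precision that it could have with no extra patient or measurement.

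**Working it through.** **Inputs from section 2.11.** Expected difference 0.13; value of 0.04 read as a superiority margin; SDs 0.19 (treatment) and 0.11 (control); alpha 0.025; beta 0.2; 48 per group before and 60 per group after 20% dropout.

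**Step 1: reproduce the plan's sample size.**
- Difference beyond the margin: 0.13 − 0.04 = 0.09.
- Root-mean-square SD: √((0.19² + 0.11²)/2) = √(0.0482/2) = 0.1552.
- Normal formula, one-sided 0.025, power 0.80: n = 2 × 0.1552² × (1.960 + 0.842)² / 0.09² = 46.7, so 47. With the t distribution it is 48.
- Dropout: 48/(1 − 0.20) = 60 per group, 120 in total.

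The variants do not fit: two-sided 0.025 gives 57 (normal) or 59 (t), and no margin gives 23 or 24. So the plan's figure is an unadjusted two-mean comparison against a margin of 0.04 at one-sided 0.025. Its power at 48 per group is 80.3%.

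**Step 2: power with ANCOVA on baseline ABI and centre.** Let rho be the correlation of baseline with 12-week ABI. The documents do not give it, so a range is shown. Section 2.11 also does not say whether the SDs are of ABI values or of change, so both readings are shown. Three degrees of freedom are spent (baseline and two centre terms).

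- SDs of ABI values: residual variance is multiplied by 1 − rho².
- SDs of change: change has variance 2σ²(1 − rho) and the ANCOVA residual has σ²(1 − rho²), with equal variance at both times. The factor relative to a t test on change is (1 + rho)/2.

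| rho | Factor, value SDs | Power | Factor, change SDs | Power |
|---|---|---|---|---|
| 0.3 | 0.91 | 83.8% | 0.65 | 93.6% |
| 0.5 | 0.75 | 90.1% | 0.75 | 90.1% |
| 0.7 | 0.51 | 97.6% | 0.85 | 86.2% |
| 0.8 | 0.36 | 99.7% | 0.90 | 84.2% |

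The two readings meet at rho = 0.5. Below that the gain is larger for change SDs; above it, for value SDs. With value SDs and rho = 0 nothing is gained, and the three degrees of freedom cost almost nothing (80.2% against 80.3%).

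**Step 3: error rate from choosing among tests at one visit.** Simulation under no effect: 48 per group, three centres with no true centre effect, equal variances, each test at one-sided 0.025, 10,000 runs per row. Each test alone rejected in 2.2% to 2.8% of runs.

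| rho | Best of t test, centre-adjusted ANOVA, ANCOVA |
|---|---|
| 0.3 | 3.2% |
| 0.5 | 3.8% |
| 0.7 | 4.6% |
| 0.8 | 4.6% |

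If only the t test and the ANCOVA are in the choice, the rate cannot exceed these values. The nominal 2.5% therefore becomes about 3–5%.

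**The case against.** The strongest defence is that the paragraph has an implied order. It first lists generic methods by data type, then states that the trial is multi-centre, gives centre-adjusted counterparts, and ends by comparing efficacy with the centre effect removed. On that reading the adjusted analysis is the efficacy comparison, and its exact form may be left to an analysis plan that is not shown. This is a fair reading, but it is not stated. It also leaves ANOVA and ANCOVA side by side with no covariate. An analysis plan would have to overrule one printed statement, not merely add detail.

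Three stronger readings are tempting and are not supported:

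- **That the plan ignores baseline ABI.** Section 2.2 speaks of changes from baseline. If the t test is run on change, baseline is used, though less efficiently than in ANCOVA.
- **That ANCOVA is meant only as a centre adjustment.** ANOVA can already carry centre as a factor, so naming ANCOVA separately suggests a covariate, plausibly baseline. The text neither says so nor excludes it.
- **That the choice of test inflates error to around a quarter.** Accepting either test at any of the five post-baseline visits gives about 27% at two-sided 5%, but ANCOVA alone over five visits still gives 19–21%. Most of that figure is the choice among visits. Similarly, about 8% for either test at week 12 is two-sided, and about half of those rejections would favour placebo. On the plan's one-sided scale the figure is about 3–5%.

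**Conclusion.** The point holds as a matter of specification. Section 2.12 gives the primary ABI to more than one test, does not say which decides, and includes one that cannot deliver the centre-adjusted comparison promised in the same paragraph. This does not depend on any assumed number.

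The size is moderate. The cost in false positives is roughly one to two percentage points above one-sided 2.5% at a single visit, under the simulated conditions. For rho between 0.3 and 0.7, power at 48 per group rises from 80% to between 84% and 98% with value SDs, or between 94% and 86% with change SDs compared with a t test on change. These figures assume the same correlation in both groups, the plan's own difference and SDs, and a rho that the documents do not give. ANCOVA gains on both readings over that range, but how much cannot be settled from the protocol. The trial remains sound if one analysis is fixed before unblinding.

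**What to change.** Replace the overlapping statements in section 2.12, or settle them in the analysis plan before unblinding, with one primary analysis:

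- Week-12 ABI in the full analysis set, by ANCOVA with treatment, baseline ABI and centre.
- Report the adjusted difference with its 95% confidence interval and claim superiority only if the lower limit exceeds 0.04, so that the decision rule matches section 2.11. The lower limit of a 95% interval corresponds to the one-sided 0.025 that reproduces the sample size.
- Label the t test and ANOVA as descriptive, or delete them for ABI.
- As a reasonable precaution, use heteroscedasticity-robust standard errors, since the planning SDs are 0.19 and 0.11.

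Naming week 12 also matters: a single ANCOVA removes the choice among tests but not the choice among the five post-baseline visits.

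The cost is wording only. Baseline ABI and centre are already collected, and no patient, visit or measurement is added.

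### ABI is measured at five post-baseline visits, but the named tests do not use these values jointly, so follow-up contrasts can be biased in either direction if loss depends on ABI

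*Protocol article*

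**What the plan says.** Section 2.10.1 of the protocol article sets the schedule of the primary outcome: "ABI will be measured before treatment and after 12-week treatment and every 12 weeks during follow-up observation, 6 times in total". Section 2.2 places the follow-up: "participants will be followed up four times at the 12th, 24th, 36th, and 48th weeks" after the end of treatment. That gives one baseline and five post-baseline values per participant, at weeks 12, 24, 36, 48 and 60 from the start of treatment. Section 2.2 also says that changes from baseline in the lower-extremity artery measures will be evaluated.

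For continuous data, section 2.12 names three kinds of method:

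- between arms: "Comparisons between groups of measurement data will be conducted by using independent-sample" t test;
- within arms: "within group differences will be tested with paired" t test;
- for the multi-centre setting: "analysis of variance (ANOVA) and an analysis of covariance (ANCOVA) will be used for measurement data".

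No time factor, arm-by-visit term or repeated-measures model is named. On analysis sets the section says "Full analysis set will analyze with intention-to-treat (ITT"), and a per-protocol set is analysed as well. Dropout appears only in section 2.11, where the sample size is raised "taking into account a dropout of 20"%.

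**The concern.** The follow-up after treatment can show whether an effect on ABI persists. A t test takes one value (or one change) per person. ANCOVA in its usual form takes one outcome value plus baseline. Applied visit by visit, neither uses the intermediate ABI values of someone who has left, although those values say something about where that person was heading.

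This matters only if leaving is related to ABI. That is plausible here but not stated. Section 2.10.4 counts occlusion, ulcer, gangrene and cardiovascular death as endpoint events, and section 2.8 removes unblinded participants and ties unblinding to adverse events. Participants who deteriorate may therefore be the ones without a later ABI. If so, a late contrast among those observed mixes the time course of the effect with selection.

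**Working it through.** **Step 1. The plan's own figure.** Section 2.11 gives a difference of 0.13, a margin of 0.04, SDs of 0.19 and 0.11, α = 0.025 and β = 0.2. Read as one-sided superiority by a margin:

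n = (0.19² + 0.11²)(1.960 + 0.842)² / (0.13 − 0.04)² = 0.0482 × 7.85 / 0.0081 = 46.7, so 47 per arm.

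The t-based calculation needs 48 (power 0.80). Then 48 / (1 − 0.20) = 60. The stated 48 and 60 reproduce. With 20% loss, 60 × 0.80 = 48 per arm remain, so planned power is not the issue.

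**Step 2. Data against methods.** There are five post-baseline ABI values per person. The methods named are t tests and ANOVA/ANCOVA, with no visit term. Nothing named links the visits in one model.

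**Step 3. Size at week 60 under ABI-dependent loss.** Settings: 60 per arm, 20% loss by week 60, loss after week 12 depending on the last observed ABI, correlation of about 0.87 between adjacent visits, true week-60 difference 0.05. The 60 per arm, the 20% and the SDs 0.19/0.11 come from section 2.11. Assumed are the correlation, the strength of the dependence, the 0.05, placing the full 20% at week 60, and treating 0.19/0.11 as SDs of ABI itself. The ranges run over increasing dependence.

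| Method | Common SD 0.15 | SDs 0.19 / 0.11 |
|---|---|---|
| t test, raw ABI | 0.036 to 0.046 | 0.061 to 0.071 |
| ANCOVA on baseline | 0.043 to 0.048 | 0.055 to 0.060 |
| All-visit likelihood-type estimate | 0.050 to 0.051 | 0.050 to 0.051 |

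Change-from-baseline t tests gave 0.044 to 0.051 across the two SD settings.

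The sign turns on the SDs. With equal SDs, the arm with lower ABI loses more of its low values, its observed mean rises more, and the contrast shrinks. With 0.19 against 0.11, removing low values lifts the mean of the more variable treatment arm more, and the contrast grows.

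**Step 4. Second check, large samples.** Here the true difference at the last visit is 0.13 unless stated, with 20% loss per arm unless stated. The assumed within-patient correlation is 0.5 to 0.8 where a range is shown, and 0.7 in the equal-SD and waned rows. SDs are 0.19/0.11 except where equal.

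| Loss pattern | t test | ANCOVA |
|---|---|---|
| Unrelated to ABI | 0.131 | 0.131 |
| Low ABI leaves, both arms | 0.146 to 0.154 | 0.136 to 0.138 |
| Low ABI leaves, both arms, equal SDs | 0.131 | 0.130 |
| Low ABI leaves, 10% treatment and 30% placebo, equal SDs | 0.104 | 0.121 |
| Opposite selection in the two arms | 0.068 to 0.090 | 0.109 to 0.115 |
| Low ABI leaves, both arms, effect waned to 0 | 0.021 | 0.007 |

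The all-visit estimate stayed within about 0.001 of the truth in every row. At week 12, before any loss, all methods agreed.

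**Step 5. Against sampling error.** At week 60, ANCOVA is off by at most 0.060 − 0.050 = 0.010, with a standard error of about 0.027 (0.010 / 0.027 = 0.37). The change-score t test is off by at most 0.050 − 0.044 = 0.006, with a sampling SD of about 0.031 (0.006 / 0.031 = 0.19). Under random loss, the repeated-measures standard error is about 3% below ANCOVA's and 16% below that of the raw t test.

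**The case against.** The strongest defence is that the plan does not prescribe a completers-only analysis. Section 2.12 states intention-to-treat on the full analysis set. How missing values enter that set may stand in a full protocol or SAP that is not shown, and its absence from an article is no finding. That stands. A reader might infer that earlier ABI values are discarded and that the stated ITT principle is breached. The text supports neither. Nor does it call ANOVA or ANCOVA single-visit; it simply gives them no visit structure.

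A reader might also infer that the follow-up contrasts will misstate how long an effect lasts, or will understate it. This is not supported either. Without ABI-dependent loss there is no bias. With it, the direction reverses between a common SD and the protocol's own SDs. The 20% is an overall sample-size allowance, tied to no visit and no arm.

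Finally, the named methods can do reasonably well. Section 2.2 speaks of change from baseline, and change-score t tests and ANCOVA stay close to the truth relative to their standard errors. This limits the importance of the point. It does not remove it, because the methods as written leave the repeated values of the primary outcome unconnected and a better choice costs almost nothing.

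**Conclusion.** The point holds as a modest improvement to the analysis of the primary outcome. The article fixes methods for measurement data that do not use the five post-baseline ABI values jointly. If loss after week 12 depends on ABI, follow-up contrasts in those observed can be biased up or down. Against a true week-60 difference of 0.05, the illustrative error is up to about 0.02 for the t test on raw ABI, 0.01 for ANCOVA and 0.006 for change scores. An all-visit likelihood-type estimate stays at 0.050 to 0.051. These sizes rest on the assumed correlation, dropout slopes and timing of loss, none of which the article gives. The week-12 contrast is unaffected if loss comes later, and the planned sample size is not affected.

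**What to change.** In section 2.12, state for ABI one likelihood-based mixed model for repeated measures on all randomised participants with any post-baseline ABI. Include arm, visit, arm-by-visit, centre and baseline ABI-by-visit, with an unstructured covariance allowed to differ by arm, given the unequal SDs in section 2.11. Read the arm contrast at each visit from that model. Use the same model for the Doppler measures, which have four time points (section 2.10.2).

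The cost is analysis programming in the SAS package already named, with no added visits or participants. The model relies on missing at random and does not resolve ABI that is missing because a participant has died. The gain in precision over ANCOVA is only about 3%, so the main benefit is protection against ABI-related loss.
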